## Abstract

**Background:**

Substance use among adolescent girls is associated with numerous risk characteristics, including engaging in sexual risk behaviors, which can lead to HIV and sexually transmitted infection (STI) diagnoses. This is an important phenomenon to target as there is a significant race-gendered paradox that occurs when Black girls use and misuse drugs. When misuse occurs among this group, they are more likely to face harsher consequences and worse health outcomes than boys and other ethnic-minority girls. Therefore, there is a need to understand the risk and protective factors of drug use and sexual risk behaviors among Black girls and develop a robust intervention that can cater for this group.

**Objective:**

We propose the development of a strengths-based prevention education intervention for Black girls between the ages of 13 and 18 years to promote protective factors.

**Methods:**

A sequential, mixed methods study will be conducted, and we will use the first 3 steps of the ADAPT-ITT (assessment, decision, adaptation, production, topical experts, integration, training, testing) framework to begin the development of the intervention. Three aims will be described in this protocol. First, aim 1 is to explore sociocultural risk and protective factors among Black girls between the ages 13 and 18 years in drug use and HIV/STI prevention using focus group methodology and surveys. We will conduct at least 10 focus groups to include up to 75 Black girls or until we reach saturation. Our target sample size for the quantitative portion of the study will be 200 participants. Aim 2 will focus on deciding upon an intervention based on findings from aim 1 and forming a youth advisory board to guide intervention development. Aim 3 will be to conduct a pretest of the intervention with the youth advisory board to determine if the intervention is feasible and will be accepted by Black girls.

**Results:**

The study is part of a 2-year research pilot study award from the National Institutes of Mental Health. Data collection for this study began in October 2021. For aim 1, data collection is 95% complete. We expect to complete all data collection for aim 1 on or before May 30, 2023. Study activities for aim 2 are occurring simultaneously as data are being collected and analyzed and will be completed in the summer of 2023. Study activities for aim 3 will begin in the fall of 2023.

**Conclusions:**

This study will be one of the few interventions that address both sexual health and drug use together and cater to Black girls. We anticipate that the intervention will be beneficial for Black girls across the nation to work on building culturally appropriate prevention education and building peer social supports, resulting in reduction or delayed substance use and improved sexual health.

**Trial Registration:**

ClinicalTrials.gov NCT05014074; https://clinicaltrials.gov/ct2/show/NCT05014074

**International Registered Report Identifier (IRRID):**

DERR1-10.2196/45007

## Introduction

Despite substantive literature on the relationship between adolescent drug use and sexual risk behavior, gaps in prevention research may continue to place Black girls between the ages of 13 and 18 years in the United States at risk. Historically, girls of all racial and ethnic groups in the United States have had lower drug use rates than boys [1]. However, over the past decade, the prevalence of smoking cigarettes, drinking alcohol, and using illicit drugs such as marijuana has increased among adolescent girls, and specifically increased as they get older [2,3]. In the past decade, Black girls have begun to engage in substance use more frequently and at rates similar to their male counterparts [2]. This is concerning because drug use among adolescent girls is linked to a variety of risk factors, including engaging in sexual risk behaviors [4,5]. According to the 2019 Centers for Disease Control and Prevention Youth Risk Behavior Survey, while cigarette use is almost nonexistent for this group, 38.6% of Black girls admitted to using electronic vapor products, with 17% of them using within the past 30 days. Similarly, 37% of Black girls in the study used marijuana, with 24.8% using marijuana within the past 30 days [2]. The rates of marijuana among Black girls have also increased significantly from early to late adolescence [6,7]. Black girls may face a significant “gender paradox” where although they are less likely to use substances than boys and other ethnic-minority girls, they tend to face more negative health consequences from use [8].

Black girls are more at risk of being persuaded to engage in sexual risk behavior such as drinking alcohol or using drugs before having sex, having sex without a condom, and having multiple sexual partners than their White counterparts [9]. These behaviors may be the direct consequence of belonging to multiple marginalized groups (eg, race, ethnicity, class, and gender), resulting in intersecting multiple levels of oppression [10]. Such behaviors may arise from the historical and contextual factors of trauma, gendered racism, and sexual exploitation that are pervasive in the lives of Black girls [11-13]. Lack of discussion and knowledge of HIV/AIDS prevention strategies, limited or nonexistent community-based preventive resources, and gender- and racial-specific behavioral interventions in urban, underresourced communities can significantly contribute to increases in sexual risk behaviors [14,15]. Sexual health disparities and drug misuse that affect Black girls not only produce poor health outcomes but can also contribute to educational inequities [16], increases in school suspension rates [17], criminal involvement [18], income inequality [19], and sexual victimization [20].

The multiple marginalized identities of Black girls place them at increased risk of early sexual debut (ie, having sex at or before the age of 14 years), making them more susceptible to condomless sex and having partners that encourage sexual risk behaviors and making them more likely to be sexually abused, which increase their risk for HIV and sexually transmitted infections (STIs) [14,21]. In one study, the authors found that among sexually active Black girls between the ages of 14 and 19 years, 48% were diagnosed with at least 1 sexually transmitted infection [22]. Being diagnosed with an STI places individuals at an increased risk of contracting HIV [23]. In addition, adults living with HIV/AIDS are more likely to engage in risky sexual behavior during adolescence [24]. As Black women currently represent 61% of women living with HIV/AIDS [25], it is crucial to intervene with Black girls in order to provide them with prevention strategies that can be used as they transition into adulthood.

Although HIV and drug abuse prevention initiatives for adolescents exist, many are homogeneous, aim to be generalizable in nature, and do not consider unique racial and gender differences in risk and protective factors [26]. Furthermore, there are very few integrated HIV and drug abuse prevention interventions for Black girls [27]. As age can limit mobility geographically, which may then contribute to the further marginalization of Black girls due to limited power and dependency on others [28]. Multiple contextual factors that are present in the lives of Black girls are often ignored, thus leaving many strategies that are embedded in prevention interventions, such as educational components that do not center the lived experiences of Black girls, not helpful for this group [27]. Researchers have called for HIV and drug use prevention research that uses an intersectional framework to examine how multiple identities interact to have an impact on attitudes and behaviors [29,30].

This study protocol is describing the formation of a mixed methods study called “The Dreamer Girls Project,” which will first understand the challenges and protective factors present in the lives of Black girls related to substance use and sexual health and then use the findings to develop a strengths-based prevention intervention. The study team will work collaboratively with a youth advisory board and use formative data collection to inform the development of the intervention. The study aims are shown in Textbox 1.

This study has the potential to provide new information about risk and protective factors for Black girls and strengths-based strategies that can be infused in HIV, STI, and drug use prevention for Black adolescents between the ages of 13 and 18 years.

Study aims.Aim 1: Understand sociocultural risk and protective factors among Black girls between the ages 13 and 18 years in drug use and HIV/STI prevention using focus group methodology and surveys.Aim 1a: Quantify the prevalence rates of drug use and behaviors associated with HIV risk among Black girls aged 13-18 years.Aim 2: Decide upon an intervention based on findings from aim 1 and form a youth advisory board to guide intervention development.Aim 3: Assess the feasibility of the intervention through theater testing.

## Methods

### Conceptual Framework

The study will use intersectionality theory as a theoretical framework to guide the formative phase and overall development of the intervention [31-33]. Our usage of intersectionality theory will incorporate a culturally relevant perspective that includes the voices of Black girls, allowing them to redefine themselves, include discussions around protective factors that they themselves perceive as beneficial in their lives, and celebrate supportive structures that nurture their ability to be resilient. An intersectional perspective, therefore, provides a unified lens through which to view health disparities and develop interventions that are more responsive to race, ethnicity, gender, age, and class [28]. Intersectionality functions as a framework in this study to understand the experiences of Black girls, who possess a different social location than Black women based on their age and cognitive and psychological development. In addition, because an intersectional perspective can be strengths based, it moves the blame away from individual behaviors to systemic and contextual factors that have historically placed Black girls at risk. The framework considers the cultural and historical context of Black girls that influences their susceptibility and exposure to drug use and sexual risk behaviors, as well as highlights the significance of systemic racism, classism, and misogyny within the United States as contributing factors to their exposure. Such a framework has been useful not only in designing and guiding social programs but also in developing ethnic, racial, gender, and class-responsive research for girls. It is to be acknowledged that Black girls are not a homogenous group, which means that significant within-group differences will exist. Therefore, the use of intersectionality theory as a framework allows for our study team to account for those differences in order to make interventions more appropriate to the experiences of Black girls [31].

### Study Design

We will conduct an exploratory, sequential mixed methods study. The protocol is registered on ClinicalTrials.gov (NCT05014074) and was approved by Yale University Institutional Review Board.

### Eligibility

Adolescent girls who identify as (1) Black, (2) identify as female, (3) are between the ages of 13 and 18 years, (4) can speak and understand English, and (5) live in the United States will be allowed to participate in this study.

### Ethics Approval

All procedures performed in studies involving human participants are in accordance with the ethical standards of the institutional and national research committee, the 1964 Helsinki Declaration and its later amendments, or comparable ethical standards. The study was funded by the National Institute of Mental Health (R25MH087217) and approved by the Yale University Institutional Review Board in 2020 (IRB-2000026660). Due to the sensitivity of the research questions, we requested that written parental consent be waived for the young participants. All youth who participate in the study (including focus groups and completing surveys) will receive a youth information sheet and parents and guardians will receive a parent information sheet. Youth must give verbal consent in order to participate in the study. We will obtain informed consent from all girls who meet the eligibility criteria and want to participate before they are enrolled in study activities.

### Recruitment

Purposive sampling for focus group recruitment will be used to ensure a representation of different subgroups of Black girls. The research team has relationships with community-based organizations in New Jersey and organizations that serve Black girls across the nation. Flyers will be given to program administrators at these organizations to disseminate to interested participants. Flyers for the recruitment of focus groups will also be posted on social media sites such as Facebook, Instagram, and Twitter. All girls who are interested in being a part of the focus groups will have to complete an eligibility form on Qualtrics (Qualtrics International Inc), which will ask for demographic information and contact information. Only girls who identify as Black and female, are between the ages of 13 and 18 years, and live in the United States will be allowed to participate. Research staff will contact eligible participants and will inform them of the purpose of the study and will screen them to confirm that they are eligible to participate based on inclusion criteria. Potential participants will be told that all data will be kept anonymous and confidential and that a monetary incentive of US $30 will be provided for participants who complete the focus group. Potential participants for the qualitative component of this study will also be informed that their responses to questions will be recorded. Upon confirmation of their desire to participate, they will be given a date, time, and Zoom (Zoom Corp) link if web-based or a physical location if appearing in person. The institutional review board has approved this study and agreed to waive parental consent due to the sensitivity of the topic. Youth assent will be obtained verbally. All youth and parents and guardians will be provided an information sheet regarding their daughter’s participation in the study. All participants and parents and guardians of participants younger than 18 years will be told that they can opt out at any time during the study. Community organizations who are able to provide us with space for in-person focus groups will receive honorariums. Recruitment for survey data collection will involve sharing the survey link on various social media platforms and community organizations that serve Black girls. Only girls who identify as Black and female, are between the ages of 13 and 18 years, and live in the United States will be allowed to complete the survey. All participants who completed the survey were compensated with a US $10 gift card.

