Data collection will involve in-depth focus groups to be conducted in a group setting at a community partner’s location sites (mainly in New Jersey due to the study team’s relationships with New Jersey–based community organizations) and web-based groups will be conducted on Zoom. Research in web-based settings has been increasing due to the COVID-19 pandemic and may continue to be a major platform to connect with participants. Research conducted in web-based settings has been established as effective venue for research on multiple content areas [37]. Efforts will be made to place participants into groups that are separated by demographic variables such as age or religion (ie, aged 13-15 and 16-18 years) as it is recommended to group individuals with similar life experiences for optimal focus group dynamics. Each focus group will be audio recorded, transcribed by trained research assistants, and entered into NVivo 11 (QSR International), a qualitative data analysis software package. Focus groups will aim to uncover how Black girls view substance use and sexual risk behavior in their community. Questions that will be discussed in the focus groups are (1) How do race, gender, and class impact views on drug use and sexual risk behavior among Black girls? (2) How do Black girls view their identity and expectations that they perceive from society? (3) What are the risk factors of engaging in drug use and sexual risk behavior that are specific to Black girls? (4) What are protective factors and what do they look like? and (5) What would a successful prevention intervention look like for Black girls in various communities? While 3 or 4 focus groups are recommended for saturation [38], we aim to conduct at least 10 focus groups or until no new data emerge from focus group discussions.

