After focus groups are conducted and before the analysis begins, facilitators of the focus groups will participate in debriefing meetings. These meetings will provide a space for facilitators to process each focus group and discuss possible issues of countertransference that may have occurred. This is necessary as we want to minimize any potential to influence the results of the study. In addition, the debriefing meetings provide facilitators the space to discuss their feelings and emotions that arose during the groups. The data analysis team will include at least 3 research assistants and the study PI who has experience in analyzing qualitative analysis and leading qualitative studies. To establish confirmability the research team will code all of the transcripts. Data will be coded using NVivo version 11. Data from the interviews will be first analyzed by interviewers using open coding, whereby concepts were identified and labeled as they emerged from the data and across the focus groups. Each member of the research team will read and reread all the transcripts and develop initial codes in isolation. During weekly research meetings, the initial codes will be reviewed and discussed. Using multiple coders provides insight into finding consistency and minimizing researcher bias [42]. The team will triangulate codes, notes, and memoranda of analyses until >95% substantive agreement is achieved. Prevalent codes (based on the frequency in which a code is used by participants across and within groups) will be grouped by similarity and relevance into themes and subthemes. To increase the rigor of the study, the researchers intend to use prolonged engagement, regular team debriefings, and member checking with participants [43]. Participants of the focus groups will be asked if they are interested in being a part of the youth advisory board. The youth advisory board will be developed for the sole purpose of confirming the findings and developing the intervention. We will aim to recruit 8-10 youth upon completion of the qualitative portion of the study.

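### Focus-group recruits are told that all data will be anonymous, but the focus-group procedures make anonymity impossible

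*Protocol article*

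**What the plan says.** The Recruitment section gives the assurance: "Potential participants will be told that all data will be kept anonymous and confidential". The sentence continues to the US $30 payment for completing a focus group, so girls considering a focus group are plainly among those addressed. The promise covers all data and names two properties, anonymity and confidentiality.

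The article describes these steps for the same girls:

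- **Recruitment:** an online eligibility form, "which will ask for demographic information and contact information".
- **Recruitment:** "Research staff will contact eligible participants" to explain the study and confirm eligibility. Those in the qualitative component are also told that "their responses to questions will be recorded".
- **Procedures:** data collection by "in-depth focus groups to be conducted in a group setting", at community partners' sites (mainly in New Jersey) or on Zoom.
- **Procedures:** "Each focus group will be audio recorded, transcribed by trained research assistants".
- **Data Analysis, Aim 1a:** rigour is to be supported by "prolonged engagement, regular team debriefings, and member checking with participants". Focus-group participants will also be asked about joining the youth advisory board, for which 8-10 girls are sought once the qualitative portion is complete.

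Ethics Approval and Recruitment say that parental consent was waived because the topic is sensitive. Youth agree verbally, and youth and parents or guardians receive information sheets.

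**The concern.** Anonymous and confidential mean different things. Data are anonymous when nobody, the research team included, can tell whose they are. Data are confidential when the team knows but undertakes not to disclose. The article promises both for all data and then sets out a process in which staff and fellow participants know who is speaking.

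What is at stake is mainly the quality of each girl's agreement to take part. Participants are 13 to 18 years old, the subject is drug use and sexual risk, and parental consent is waived. The girl's own decision is therefore a central protection, and it is made on the strength of this statement. If staff follow the plan as written, they give an assurance that the study cannot keep. No estimate, sample size or analysis depends on it.

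**Working it through.** No arithmetic tests the claim itself. The check sets the assurance against each described step.

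1. **Screening form.** Contact details are collected before enrolment, so the team holds an identifier for each focus-group recruit. This is incompatible with anonymity towards the team.
2. **Individual contact.** Staff speak or write to each eligible girl and assign her a session. The link between person and session is known.
3. **Group setting.** Each girl speaks in front of others. This is incompatible with anonymity towards peers, and no later handling of transcripts can undo it.
4. **Audio recording.** A voice recording of a scheduled group of known girls is identifiable material, at least until it is transcribed and destroyed.
5. **Member checking and board invitation.** The article does not give the timing or route of either. The board is to be recruited after the qualitative portion, which implies that the team can still reach named participants. Member checking could in principle take place within a session, so it adds less weight.

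Steps 1 to 3 are enough on their own.

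**Scope.** The next sentence in Recruitment singles out the qualitative component for the notice about recording, so the assurance may have been meant for everyone. On either reading it includes the focus-group girls.

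**Number affected.** The target is at least 10 groups and up to 75 girls. At 10 groups and 75 girls the average group is 75 / 10 = 7.5, so about 7.5 − 1 = 6.5 peers hear each speaker. More groups or fewer girls would lower this.

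**Number still reachable.** Aim 1 data collection is reported as 95% complete, without a split between focus groups and survey. If the remaining 5% were counted over both targets, it would be 0.05 × (75 + 200) = 13.75, about 14 participants. If it applied to the focus groups alone, it would be 0.05 × 75 = 3.75, about 4. Because the design places focus groups before the survey, it could be none. These are illustrations under stated assumptions; the article does not give the count.

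**The case against.** The strongest reply is that this is one imprecise word in a condensed article. Recruitment summarises what girls are told; the information sheets are not shown and may describe the limits of confidentiality in a group. The word may have been meant for de-identified transcripts. The girls know that they are joining a group and are told of the recording. Participants, and the parents or guardians of those under 18, are told that they can opt out at any time. The ethics board approved the study.

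Part of this stands. The absence of detail on storage, coding or destruction of recordings is not a finding, and nothing is concealed about the recording. But the article states what will be said, and its own procedures contradict it. De-identifying transcripts would not make a peer group anonymous. If the sheets are worded correctly, girls receive two conflicting messages. Ethics approval does not remove the conflict.

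A reader might infer stronger points that the article does not support:

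- *That girls are asked for personal drug or sexual histories in the group under a false promise.* The five listed questions concern views, identity, risk and protective factors, and the shape of an intervention. Personal disclosure is foreseeable but not solicited. The measures of 30-day drug use and sexual risk behaviour belong to the survey.
- *That the survey is not anonymous either.* It is reached by a shared link and could be anonymous. How the US $10 gift card is delivered, and whether it is linked to answers, is not stated and may be left to the full protocol.
- *That survey takers cannot give the required consent.* Ethics Approval says "Youth must give verbal consent in order to participate in the study" and no contact with survey takers is described, but consent mechanics are commonly left out of an article.
- *That all those affected are minors.* 18-year-olds are eligible.

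**Conclusion.** The contradiction holds for the focus groups. The plan tells recruits that their data will be anonymous, and the plan's own steps show that they will not be. It affects up to 75 girls and concerns the accuracy of what they are told when they agree to take part. Actual harm is not shown, nor is any effect on the answers given. The conclusion assumes only that the Recruitment text reflects what is actually said to girls and that the procedures run as described. It should be corrected because parental consent is waived and the correction is cheap, but its practical reach within aim 1 is small at this stage.

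**What to change.** For the focus groups, delete the word anonymous from the recruitment statement and from any script or sheet that repeats it. Replace it with wording to this effect: the study team keeps what you say confidential; the team holds your contact details and a recording of the session; other girls in the group will hear what you say, and the team cannot guarantee that they will keep it private.

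Use the corrected wording in any remaining sessions, at member checking, in advisory-board contacts, and in the feasibility trial and larger trial that the Conclusions foresee, where the present script might otherwise be reused.

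The cost is a small wording amendment through the ethics board. Its drawback is that few aim 1 participants remain to benefit. No design, sample-size or analysis change follows.
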